#### Neck motor control exercises

3.4.2

The duration will consist of 12 weeks with a frequency of three times per week in the first month, two times in the second month, and once per week in the final month (24 sessions in total). Each session will include localized motor control of neck flexors and extension muscles with a duration of 30–45 min. Low‐load craniocervical exercises (head nods) will be performed in the early stages (first 6 weeks) guided by visual feedback from a pressure unit (NOD device). Higher load neck exercises will be performed in later stages (last 6 weeks). This duration of treatment is commonly used in clinical settings and has been shown to be sufficient to improve clinical outcomes (Bednarczyk et al., 2024). This exercise protocol is detailed in Supplementary Material 2 and has been successfully tested in subjects with neck pain.

### Assessments

3.5

#### EIH procedures and time points

3.5.1

On the days of assessments, participants will be instructed to refrain from additional physical exercise, caffeine, nicotine and alcohol (Vaegter et al., 2019). To evaluate the acute effects of exercise protocols, participants will be assessed before, immediately after and 15 min after a single intervention session. The sessions are part of a 12‐week exercise programme. Since both protocols progressed from light to high intensity throughout the intervention period, three time points (i.e., three sessions) were chosen for the evaluations of three different exercise intensities (low, moderate and high). For the neck motor control exercises group, sessions 3, 12 and 22 were chosen. For the AE group, sessions 3, 12 and 32. Assessors will be blinded to the treatment allocation. Those specific sessions were chosen to ensure that participants will be assessed at the beginning, middle and end of each specific protocol at low, moderate, and high intensities, respectively.

At the three time points, three measurements will be conducted. The first measurement will be collected before the intervention, the second measurement will be immediately after the end of the intervention (considering 5 min of preparation of the room) and the third measurement will be after 15 min of rest on a stretcher (30 min after intervention). During the resting time, no intervention will be performed. Considering that each measurement lasts approximately 15 min, this timeline will allow us to determine whether EIH lasted at least 30–35 min. Figure 2 describes the sequence of events.

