#### Aerobic exercise (AE)

3.4.1

AE training will consist of 12 weeks of exercise supervised by a physiotherapist with a frequency of three times per week (36 sessions in total). Overall, the session will have a total duration of 60 min and will be divided into three parts: warm‐up, main exercise period and cool‐down. The training will be performed on a cycle ergometer or treadmill (based on the participant's choice). The intensity will be based on maximum heart rate (HR_max_), heart rate reserve (HR_res_) and the subjective perception of effort (Borg Scale), which will be monitored. The Borg scale will be the main variable considered to increase the intensity of the protocol or to stop the training. The HR_max_ will be calculated by a ramp protocol for the cycle ergometer and confirmed by standard formulas.

The intensity of the AE programme will be progressively increased according to each participant's response but will be standardized as much as possible, as follows:
In the first 2 weeks, participants will start the walking/cycling programme at low intensity (at 60% HR_max_ or 9–11 on the Borg scale).At 2–6 weeks, depending on the response to the first sessions, the training will progress to moderate intensity (55–70% HR_max_ or 12–14 on the Borg scale);In the last 6 weeks, high‐intensity interval training (HIIT) will be targeted as recommended by the literature (Geneen et al., 2017). The HIIT consists of changing between moderate and high intensity for short intervals. Thus, during the first 4 min, the participant should train at high intensity (75–90% HR_max_ or 15–17 on the Borg scale), and in the subsequent 3 min, the participant should train at moderate intensity (55–70% HR_max_ or 12–14 on the Borg scale). This is done continuously until the total training time is completed (4 min × 4 times (high‐intensity training) followed by 3 min of moderate in between, totalling 28 min of active training) according to the participant's response. The intensity of the aerobic training in each session will be targeted individually with an increase of 5 W every 5 min according to the specific stage the participant is in and based on the Borg scale. Supplementary Material 1 describes the full protocol for the aerobic training group, which will also perform stretching exercises before and after the intervention.

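### Neck session 12 is presented as the moderate-intensity assessment, but by the protocol's own schedule it falls in week 4 of a six-week low-load stage

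*Protocol article*

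**What the plan says.** Section 3.5.1 (EIH procedures and time points) gives the reason for three assessed sessions: both programmes progress from light to high intensity, and one session is to represent each of three levels. Participants are to be "assessed at the beginning, middle and end of each specific protocol at low, moderate, and high intensities, respectively". The sessions are then named: "For the neck motor control exercises group, sessions 3, 12 and 22 were chosen", and "For the AE group, sessions 3, 12 and 32".

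Section 3.4.2 (Neck motor control exercises) sets the neck schedule at "three times per week in the first month, two times in the second month, and once per week in the final month", 24 sessions over 12 weeks. It describes two stages of load. The low-load craniocervical exercises "will be performed in the early stages (first 6 weeks"), and then "Higher load neck exercises will be performed in later stages (last 6 weeks"). It describes no moderate stage and refers to Supplementary Material 2 for detail.

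Section 3.4.1 (Aerobic exercise) runs "with a frequency of three times per week (36 sessions in total") over 12 weeks. It has three stages: low intensity in the first two weeks, moderate in weeks 2 to 6 depending on response, and high-intensity intervals in the last six weeks.

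Objective 2 (section 2) asks about the EIH response at different time points of the 12-week programme. Section 3.7 (Analyses plan) addresses it with exploratory mixed models of EIH that compare treatment groups and three training stages, named beginner, intermediate and advanced.

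**The concern.** The assessed sessions are justified by the intensity each is meant to represent. If neck session 12 belongs to the same load stage as session 3, the neck arm has no assessment at a moderate level as its programme is described, and the middle visit means something different in each arm.

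Two results would be open to misreading. First, the group contrast at the intermediate stage would set moderate aerobic exercise against neck exercise still in its low-load stage, under labels suggesting that the levels match. Second, a flat neck response from session 3 to session 12 could be reported as showing that moderate neck exercise adds no hypoalgesia, when both sessions come from the same stated stage. The Introduction says that knowing which exercise parameters give the strongest hypoalgesic effect would help clinicians choose an intervention, so a wrong intensity label bears on a declared purpose of the study.

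**Working it through.** **Inputs.** Neck arm (section 3.4.2): 3, 2 and 1 sessions a week in months 1, 2 and 3; low load in weeks 1–6, higher load in weeks 7–12. Aerobic arm (section 3.4.1): 3 sessions a week for 12 weeks. Assessed sessions (section 3.5.1): neck 3, 12, 22; aerobic 3, 12, 32. A month is taken as four weeks, so that three months make the stated 12 weeks.

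**Reproducing the plan's totals.** Neck: 3 × 4 + 2 × 4 + 1 × 4 = 12 + 8 + 4 = 24, as stated. Aerobic: 3 × 12 = 36, as stated.

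**Neck sessions by week.** Weeks 1–4 hold sessions 1–12, weeks 5–8 hold sessions 13–20, and weeks 9–12 hold sessions 21–24. The low-load stage ends with week 6, so it contains 12 + 2 × 2 = 16 sessions. Sessions 1–16 are low load and sessions 17–24 are higher load.

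**Assessed sessions against stated stages.**

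| Arm | Session | Week | Level named in 3.5.1 | Stage described in 3.4 |
|---|---|---|---|---|
| Neck | 3 | 1 | low | low load |
| Neck | 12 | 4 (last session) | moderate | low load |
| Neck | 22 | 10 | high | higher load |
| Aerobic | 3 | 1 | low | low |
| Aerobic | 12 | 4 | moderate | moderate |
| Aerobic | 32 | 11 | high | high-intensity intervals |

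Five of the six labels agree with the stage descriptions. Neck session 12 does not: 16 − 12 = 4 low-load sessions are still to come.

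**Sensitivity to the assumptions.** The placement does not depend on the length of a month. At three sessions a week, session 12 closes week 4 (12 ÷ 3 = 4) whenever the first month has at least four weeks. It does assume attendance close to schedule. If sessions are numbered as attended, a woman would reach session 12 after week 6 only by attending at most 11 of the 16 sessions planned to that point, that is, by missing five or more.

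**The case against.** The strongest counter-argument is that objective 2 and its model are worded by time point and training stage. Neither names intensity as a factor, and the analysis is called exploratory in a 30-participant pilot without a formal sample size calculation. Objectives 1 and 3, the acute effects and the minimal important difference, do not depend on the intensity label. All of this stands, and it limits the severity. It does not remove the contradiction, because section 3.5.1 selects and names the sessions by intensity, and a reader of the results would carry those names into the stage-by-group comparison.

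A second argument is that section 3.4.2 is a summary and that Supplementary Material 2, not shown here, may grade the load within weeks 1 to 6. That cannot be excluded. The supportable statement is therefore that sections 3.4.2 and 3.5.1 disagree as written, not that no moderate step exists.

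A reader might infer more than the documents support:

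- *That the neck arm has no valid intensity levels, or that objective 2 cannot be answered.* Sessions 3 and 22 fit their labels, a low versus higher-load contrast remains, and objective 2 can be analysed by time point as written.
- *That the aerobic middle visit is also mislabelled.* Session 12 of 36 is one third of the way through, so calling it the middle is loose, but week 4 lies in the stated moderate stage. In the neck arm, session 12 of 24 is the midpoint by session count.
- *That the last visits, in weeks 10 and 11, should coincide.* Section 3.5.1 promises the end of each protocol, not a common calendar week, and both visits are in the final stage.
- *That the joint rise of load and training time is a drafting error.* It is inherent in a progressive programme, which objective 2 states openly. It is a limit on interpretation only.

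**Conclusion.** The point holds for one label. On the visible text, neck session 12 is a second low-load assessment and not a moderate one. The neck visits are low, low and higher load, against low, moderate and high in the aerobic arm. This affects one of three neck assessments for all 15 women planned in that arm, and with it the middle-visit contrast between arms and the neck change from session 3 to session 12. Neither can be read as an effect of intensity. The time-point analysis of objective 2 and the other two objectives are intact.

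The conclusion rests on four-week months, which reproduce the stated 24 sessions, on attendance close to schedule, and on section 3.4.2 being a fair summary of the detailed neck protocol. Severity is moderate: the label is a stated design property that the neck arm lacks as described, but correcting it before analysis is simple.

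**What to change.** Reconcile sections 3.4.2 and 3.5.1. If the detailed neck protocol defines a moderate step that session 12 falls in, state in the main text what makes that session moderate.

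Otherwise:

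- define the factor in the objective 2 model as visit (first, second, third), and say that it does not stand for a common intensity scale across arms;
- report the neck visits by load stage (low, low, higher) beside the aerobic stages (low, moderate, high-intensity intervals);
- state that neither the group contrast at the middle visit nor the neck change from session 3 to session 12 will be interpreted as an intensity effect.

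This costs a few sentences, with no added visit and no change to data collection. No session needs to be moved. Shifting the middle neck assessment to session 17 or later would not produce three levels: session 17 is in week 7, in the same higher-load stage as session 22, so the visits would become low, higher and higher, and the shared week-4 timing with the aerobic arm would be lost.

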**FIGURE 2 eph13772-fig-0002:**
[figure not shown]
Flowchart of study procedures.

### Outcome measures

3.6

#### Pain intensity

3.6.1

Pain intensity will be measured by the VAS in which the participants will rate the pain from 0 to 100 mm, referring to the orofacial region (TMD) and the cervical region, separately, considering that 100 indicates the ‘worst imaginable pain’ and 0 indicates ‘no pain’. The VAS has good reliability (Jensen et al., 1999), and a 19 mm reduction has been considered clinically important for women with TMD (Calixtre et al., 2020).

#### Quantitative sensory testing

3.6.2

##### PPT

The PPT is defined as the minimum pressure that induces the first sensation of pain. PPT will first be assessed on the dominant hand for familiarization. Specific muscles were selected because they are the most prone to pain in this population and will be assessed bilaterally (Figure 3) (Silveira et al., 2015):
Anterior temporalis (2 cm above the zygomatic arch).Superficial masseter (1 cm superior and 2 cm anterior to the mandibular angle).Occipital region (slightly below the superior nuchal line where the trapezius muscle inserts).Upper trapezius (halfway between the C7 vertebra and the acromion).

**FIGURE 3 eph13772-fig-0003:**
[figure not shown]
Masticatory, neck, and leg muscles chosen for assessments. (a) anterior temporalis; (b) superficial masseter; (c) occipital region; (d) upper trapezius; (e) quadriceps; (f) tibialis anterior.

Additionally, one measurement will also be taken in two muscles located in the dominant lower extremity:
Quadriceps (rectus femoris, 20 cm proximal to the base of patella) (Jones et al., 2019; Vaegter et al., 2015).Tibialis anterior (muscle belly) (Alburquerque‐Sendín et al., 2013; Ashina et al., 2006; Walton et al., 2011)

The algometer function of the NOD device (http://www.to‐nod.com/) will be used to measure PPTs and pressure pain tolerance (PPTo). The measurements will be collected in kPa and converted to kg/cm^2^. The order of locations to be tested will be randomized, and a rate of 0.5 kg/s will be used as force application (Figure 4). The mean of two PPT measurements will be considered for analysis. If the second measure differs more than 10% from the first measure, a third measure will be collected. The minimal detectable change for the PPTs of neck muscles of patients with neck pain was reported as 0.45–1.13 kg/cm^2^ and for women with TMD as 0.18 kg/cm^2^ and 0.22 kg/cm^2^ in the masseters and temporalis (Calixtre et al., 2020), respectively. The PPT measurements have good to excellent inter‐ and intra‐rater reliability (0.74–0.99) (Walton et al., 2011). Higher values mean less pain sensitivity.

**FIGURE 4 eph13772-fig-0004:**
[figure not shown]
NOD device assessment in the dominant hand (a), left anterior temporalis (b), left masseter (c), right occiput (d), right upper trapezius (e), dominant quadriceps (f), and dominant tibialis anterior (g).

#### Pressure pain tolerance

3.6.3

The pressure pain tolerance (PPTo) will be considered as the most bearable pain. Just one measurement will be collected for PPTo in each location, and this measurement will be conducted immediately after the two measurements of the PPT.

#### EIH

3.6.4

For participants with neck pain, the occipital region point will be chosen to calculate EIH, and for TMD, the masseter point will be used. Relative and absolute changes will be used to calculate EIH. The pre‐exercise PPT values will be subtracted from the post‐exercise values (Aron et al., 2024; McPhee Christensen et al., 2022). After subtracting the values, an increase in the thresholds will be considered a positive response to exercise. The difference between the pre‐ and post‐exercise values of the VASs will also be assessed.

##### Self‐perception of improvement

As an anchor measure, the Global Rating of Change Scale (GRCS) will be collected along with pain thresholds at each time point for each group (Kamper et al., 2009). This tool was designed to quantify a patient's improvement or deterioration over time, being important to determine the effect of the intervention based on the patient's perspective. Participants will classify post‐intervention effects on a 15‐point scale from −7 (a very great deal worse) to 7 (a very great deal better). The GRCS will be used to determine the clinical significance of the EIH.

### Analyses plan

3.7

All analyses will be performed by the statistical program SPSS version 26 (IBM Corp., Armonk, NY, USA) and STATA v.17 (StataCorp, College Station, TX, USA). The Shapiro–Wilk test and visual inspection of histograms and graphs will be used to verify the normality of the data. Then, descriptive statistics will be performed to characterize the sample and explore variables. The results will be presented as mean and standard deviation when the variables are normally distributed, or as median and interquartile range when the data distribution is not normal. A 95% confidence interval will be adopted. *P*‐values will be interpreted based on Sterne and Smith to determine the evidence against the null hypothesis (Sterne & Smith, 2001).

To accomplish objective (1), which is to assess the effects of a single bout of neck motor control exercises and aerobic training exercises on pain intensity, PPT and PPTo in participants with TMD and neck pain, further inferential analyses will include separate mixed‐effects models (random effect for repeated measurements per participant) for each outcome to assess the effect of the intervention (groups) over time and adjusted by other covariates. First, a fixed‐effects model for each outcome at the final evaluation that includes only the intervention groups and baseline score will be created. Then, mixed‐effects models (random effects for repeated measurements per participant and groups (intercept and slope) will be tested. Finally, these models will be expanded to include covariates (e.g., demographics, psychosocial variables). Models will be compared using the Akaike information criterion (AIC) and the Bayesian information criterion (BIC). The covariates may be dropped from the models if not required for model fit based on AIC and BIC. Model estimates and associated 95% confidence intervals (CI) will be reported.

To accomplish objective (2), the EIH response will be calculated in absolute (raw score) and relative (percentage) changes by subtracting the post‐exercise PPT and PPTo values from the pre‐exercise values. Further exploratory analyses will also be performed with mixed‐effects models considering EIH as an outcome to compare the time points of treatment (beginner, intermediate and advanced training) and group treatment.

To determine the clinical significance of EIH (objective (3)), distribution‐based and anchor‐based methods will be performed after the two modalities of exercise. Using distribution based‐methods, ES will be calculated and will be classified following Cohen's *d* formula and interpretation (large ES if >0.8; moderate, >0.5; small >0.2) (Cohen, 1988), if the data are parametric, and by Cliff's Delta, if the data are non‐parametric (Macbeth et al., 2011). Other distribution‐based methods such as those derived from standard deviation and ESs will be explored (Armijo‐Olivo et al., 2022).

The MID of the outcomes of interest (PPTs and PPTo) for EIH using the GRCS as anchor will be used (anchor‐based methods). Participants will be classified as having no improvement when their responses to the GRCS are between −7 and 0, slight improvement between 1 and 3, moderate improvement between 4 and 5, and large improvement between 6 and 7 after the treatment. Changes from baseline to after intervention and 15 min will be calculated for each one of the outcomes of interest at each of the time points collected and used for analysis. Correlations between the GRCS and each of the variables of interest will be tested. The receiver operating curve analysis will be performed to generate the MIDs. This analysis compares the values of each measure from both groups according to the GRCS: participants who did and did not show minimal improvement after treatment. This method constructs a graph of the measures’ performance in classifying the groups for each possible cut‐off point and calculates the sensitivity and specificity for all the cut‐offs. The main analysis will concentrate on calculating the minimal improvement to calculate the MIDs and differentiate the groups. Secondary analysis will include moderate and large improvement when possible. In addition, and if possible, an analysis divided by motor areas (primary and non‐primary) for each group (neck or aerobic) and each diagnosis (TMD, neck only, and both) will be addressed.

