### Participants

3.2

Women between 18 and 60 years of age, diagnosed with chronic non‐specific neck pain (as described by the IASP) and/or diagnosed with TMD according to the Diagnostic Criteria for Temporomandibular Disorders—DC/TMD (Dworkin, 2014) will be included. In addition, a baseline pain score of at least 30 points on a 0 to 100 visual analogue scale (VAS) will be required. Participants with severe pathologies (red flags) related to neck pain, reporting comorbidities (e.g., fibromyalgia), diagnosed with psychiatric disorders, and/or who received therapy within 3 months before study entry will be excluded. All participants will complete the Physical Activity Readiness Questionnaire (PAR‐Q+) to assess readiness to exercise. The Central Sensitization Inventory (CSI) recommended for patients with chronic pain will also be applied. The CSI is an easy‐to‐apply self‐report questionnaire that tracks and assesses symptoms related to overall sensory disturbances (Mayer et al., 2012).

This exploratory clinical trial aims to gather preliminary data on the safety and potential efficacy of a single bout of exercise for individuals with TMD and neck pain. Given the exploratory nature of this study, a formal sample size calculation was not conducted. Instead, the sample size was determined based on practical and logistical considerations. This exploratory study pilot will initially target 30 participants (15 per group), aiming to gain insights and assess feasibility. Based on the targeted sample size and a clinically important difference of 19 points (on a 0–100 pain scale) (Calixtre et al., 2020) with a standard deviation of 20, the study has an estimated 71% power to detect a large effect size (ES, Cohen's *d* = 0.95) using a significance level of 0.05. The recruitment rate of participants, availability of the research team, time, and resources were considered for the targeted sample size. The data collection is expected to be finished by the end of 2025. The results of this study will help to design and calculate sample sizes for future studies.

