### Allocation concealment

3.3

All participants will be randomly assigned to one of the treatment groups: neck motor control exercises or AEs by using an automated system hosted on a web platform. The randomization sequence will be stratified by chief complaint (neck pain or jaw pain) and age (18–30, 31–45, 46–60) and generated by an external party using a randomization website. The sequence generated will be automatically programmed in REDcap to allow the allocation concealment of the sequence.

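### Randomisation is stratified by chief complaint and age band, but the models need not contain either factor, because the base model omits both and any covariate may be dropped on AIC/BIC

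*Protocol article*

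**What the plan says.** In the Protocol article, section 3.3 (Allocation concealment) has the sequence "stratified by chief complaint (neck pain or jaw pain) and age", with age in three bands. That makes 2 × 3 = 6 strata.

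Section 3.7 (Analyses plan) builds the objective 1 models in steps: group and baseline score alone, then random effects, then covariates given by example (demographic and psychosocial variables). Age would count as a demographic. Chief complaint is named in no model. The removal rule is: "The covariates may be dropped from the models if not required for model fit based on AIC and BIC". It makes no exception for the stratification factors and does not say which criterion decides when the two differ.

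For objective 2 the plan describes exploratory mixed-effects "models considering EIH as an outcome to compare the time points of treatment (beginner, intermediate and advanced training) and group treatment". Session and group are the only terms it names.

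On size, section 3.2 (Participants) says: "This exploratory study pilot will initially target 30 participants (15 per group), aiming to gain insights and assess feasibility".

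**The concern.** Stratified allocation balances the groups on the strata, so differences between strata drop out of the true sampling error of the group contrast. A model without the strata leaves that variation in its residual and overstates the standard error. The error is conservative: intervals too wide, power lost. Section 3.2 says the results will inform later sample sizes, so an inflated residual SD would carry forward.

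Chief complaint has a particular role here. Section 3.6.4 takes EIH at the occiput for neck pain and at the masseter for TMD. Section 3.6.2 gives minimal detectable changes of 0.45–1.13 kg/cm² for neck muscles and 0.18 kg/cm² for the masseter, a ratio of 2.5 (0.45/0.18) to 6.3 (1.13/0.18). This does not show that complaint predicts change. It does show that raw EIH pools two measurement scales, which is a reason not to leave the term to a fit criterion.

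Separately, choosing terms on the same data makes the reported 95% interval conditional on a search that the interval ignores.

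**Working it through.** **Inputs from the Protocol article.** 15 per group; "a clinically important difference of 19 points (on a 0–100 pain scale"; "with a standard deviation of 20"; "using a significance level of 0.05"; PPT reliability 0.74–0.99 (section 3.6.2).

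**Assumptions.** The share of outcome variance explained by the strata (R²), the pre/post correlation r (0.74 is borrowed from the reliability range, which is not the same quantity), and block size (2 or 4), which the article does not give.

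**1. The plan's own figure.** Section 3.2 says "the study has an estimated 71% power to detect a large effect size". With d = 19/20 = 0.95, noncentrality 0.95 × √(15/2) = 2.60, 28 df and a two-sided test, power is 70.9%. The 71% is reproduced.

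**2. Strata left out, no baseline adjustment.** Reported SE over true SE is about 1/√(1 − R²):
- R² = 0.2: 1/√0.8 = 1.118, so 12% too large
- R² = 0.3: 1/√0.7 = 1.195, so 20% too large

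**3. Strata left out, baseline adjusted.** Let the strata explain S of the variance at both times, with overall correlation r. Residual variance is 1 − r² with baseline alone, and (1 − S) − (r − S)²/(1 − S) with baseline and strata.
- r = 0.74, S = 0.2: 0.4355/0.4524 = 0.963, partial R² 3.7%, SE ratio 1.019
- r = 0.74, S = 0.3: 0.4234/0.4524 = 0.936, partial R² 6.4%, SE ratio 1.034
- r = 0.5, S = 0.2 and 0.3: SE ratios 1.044 and 1.080

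So about 2–3% at r = 0.74, and 4–8% at r = 0.5.

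**4. The dropping rule itself.** Simulation of 5,000 trials per setting: 30 participants over six strata, R² split equally between the factors, permuted blocks, difference 19, SD 20, least squares on one endpoint, no baseline covariate. At R² = 0.3 with blocks of 2:

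| Model | True SE | Reported SE | Coverage | Power |
|---|---|---|---|---|
| Strata never entered | 6.13 | 7.30 | 97.8% | 72.4% |
| Strata forced in | 6.02 | 6.10 | 95.4% | 84.3% |
| AIC selection | 6.04 | 6.09 | 95.4% | 84.4% |
| BIC selection | 6.06 | 6.18 | 95.5% | 83.6% |

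Across all settings, selection kept coverage between 94.1% and 95.5%. The largest shortfall in the reported SE came with AIC at R² = 0 and blocks of 4: 7.12 against 7.45, or 4.4% too small. In that setting the forced model was also short (7.31 against 7.49, 2.4%), so selection accounts for roughly half of it.

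**5. AIC against BIC at n = 30.** A factor with p degrees of freedom is kept if its partial R² exceeds 1 − exp(−2p/30) under AIC, or 1 − exp(−p ln 30/30) under BIC:
- chief complaint (p = 1): 6.4% against 10.7%
- age band (p = 2): 12.5% against 20.3%

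Share of simulated trials in which at least one factor was dropped, AIC then BIC: 96% and 99% at R² = 0; 81% and 93% at 0.1; 33% and 59% at 0.3; 4% and 13% at 0.5. The partial R² of 3.7–6.4% from step 3 lies between the first two settings, so in a baseline-adjusted model the rule would usually remove at least one design factor.

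**6. Cost of keeping both.** Three df (1 + 2) leave 25. By noncentral t, power is 70.6% at R² = 0, against 70.9% unadjusted; it is 79.8% at 0.2 and 84.8% at 0.3. In the simulation at R² = 0, where groups and strata are not perfectly balanced, forcing cost about 1 point (71.4% to 70.3%, blocks of 2).

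**The case against.** The strongest reply is that the rule does little harm. AIC and BIC tend to remove factors when they predict little, and at R² of 0.3 or more selection gave power within one point of forced adjustment. That stands. A reader might infer that AIC/BIC dropping itself makes standard errors 12–20% too large. It does not: that figure belongs to strata never entered and no baseline score, whereas the objective 1 base model includes baseline, which absorbs most of what chief complaint says about pain level.

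It can also be said that the covariate list is only by example, that the objective 2 models are labelled exploratory, and that a fuller plan may exist. This stands against any complaint about an incomplete list. It does not answer the stated removal rule, which has no exception.

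A reader might go further and hold that the EIH change-score model has wrong error bars, or that change scores should give way to a model adjusted for the pre-exercise value or run on the log scale. The documents do not support this:
- Change-score intervals are valid. Simulated reported and true SE were 0.261 and 0.262 at r = 0.74, with coverage of 94.7–95.6% over r from 0.5 to 0.99.
- The precision forgone is modest: the variance ratio (1 + r)/2 is 0.87 at r = 0.74 and 0.95 at 0.9.
- Every assessed session (3, 12 and 22 or 32) follows randomisation, so its pre-exercise value may already reflect training and is not a clean baseline covariate.
- Percentage change drifts upward by about CV² under no effect (2.3% at an assumed CV of 15%), but this largely cancels in group and session contrasts when CVs are equal. Absolute change is reported as well.

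**Conclusion.** The point holds in a limited form. The design stratifies on two factors, and the analysis as written need not contain either. If they predict outcome beyond baseline and are left out, group-contrast intervals are too wide: about 2–3% in SE with baseline adjustment (r = 0.74, stratum R² 0.2–0.3), and up to about 12–20% without it. The upper figure would apply to the EIH model only if the strata explained 20–30% of the variance of the change itself, for which the article gives no evidence. The removal rule adds a small error in the opposite direction (reported SE up to about 5% too small when the factors are weak). It also leaves the final model open, because the two criteria named have different thresholds at this sample size. R², r and block size are all assumed. In a 30-participant exploratory pilot this is a modest matter of precision and pre-specification. It does not threaten validity.

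**What to change.** Add to section 3.7 that chief complaint and age band are kept as fixed terms in every group-comparison model, both the objective 1 models (including the first, with group and baseline score) and the objective 2 EIH models, and that AIC/BIC selection applies only to the other covariates. Also state which criterion decides when the two disagree.

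Both variables are already recorded for randomisation, so no new data are needed. The cost is three degrees of freedom: 0.3 points of power by formula if the strata predict nothing (about 1 point in simulation), against a gain of about 9 points (70.9% to 79.8%) if they explain 20% of the variance and nothing else is adjusted for. The gain is smaller once baseline is in the model. The EIH definition can stay as it is.
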